### Data management {19}

Data are entered anonymously. Data collection will be monitored by a clinical research assistant. When requested, the two investigators will clarify the data. Data management is under the responsibility of the University of Brasilia.

The Data Management Coordinating Center will oversee the intra-study data-sharing process, with the involvement of the Data Management Subcommittee. Only the principal investigator will be given access to all the data with a special password. Other project investigators will have direct access to their own site’s data sets and other sites’ data by request. To ensure confidentiality, data dispersed to project team members will be blinded to any identifying participant information.

### Confidentiality {27}

The final trial dataset will be available to the clinical research assistants, data managers, and statisticians, subject to professional secrecy. Data are anonymous.

### Plans for collection, laboratory evaluation, and storage of biological specimens for genetic or molecular analysis in this trial/future use {33}

N/A. No collection.

## Statistical methods

### Statistical methods for primary and secondary outcomes {20a}

The data will be analyzed using SPSS 25.0 software (IBM Co., Armonk, NY, USA).

#### Baseline analysis

The three groups will be similar in terms of disease type and periapical lesion size.

#### Main outcome analysis

The inter-group comparison of success rates will be analyzed using the Kruskal-Wallis test at 5% of the level of significance. For the missing data, the last observation carried forward (LOCF) method will be adopted to fill the validity analysis.

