### Sample size *{14}*

The determination of the sample size will be performed sequentially, with a minimum of 210 statistical units (teeth) to be recruited in the first stage, and the second stage of recruitment will be performed if the selection is insufficient to clinically and radiographically identify valid cases. This sampling will also allow the adjustment of the sample size for the intra-subject correlation of statistical units (teeth). In the first stage, 150 adults aged 18 to 60 years, with at least one tooth diagnosed with asymptomatic apical periodontitis and periradicular lesion with a diameter between 1 and 5 mm, will be recruited.

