## Sample size and statistical methods

### Sample size details

The required sample size was calculated based on the preliminary outcome parameter of success, in a sequential approach, with each clinical case (tooth) serving as the statistical unit. Clinical studies that allow us to estimate, by means of CBCT, the repair index (complete absence of periapical radiolucency), therefore the success, after endodontic treatment of teeth with apical periodontitis and periradicular lesion, state that it is necessary to have a follow-up of at least 2 years to determine the success or failure of the treatment [22, 23]. After the first year of follow-up, post-endodontic treatment, it is still possible to observe the presence of periapical radiolucency in 52 to 84% of cases [1, 24, 25]. The sample will consist of 210 mandibular molars (first or second molars), based on statistical sample calculation, considering a power of 80%, an alpha value of 0.05, and an effect size of 20%. All patient characteristics at the beginning of treatment, such as age, gender, lesion size, among others, will be considered in the statistical analysis, in order to confirm the randomization of groups and the possible confounding effect of these characteristics.

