### Methods for additional analyses (e.g., subgroup analyses) {20b}

N/A. No additional analyses are planned.

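### The primary test treats 210 teeth from 150 patients as independent; its 5% level is inflated if whole patients are randomised, and the protocol states the randomisation unit two ways

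*Protocol article*

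**What the plan says.** All references are to the protocol article.

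- **Main outcome analysis** names one test for success: "The inter-group comparison of success rates will be analyzed using the Kruskal-Wallis test at 5% of the level of significance".
- **Sample size details** sets the unit, "with each clinical case (tooth) serving as the statistical unit", and the number: "The sample will consist of 210 mandibular molars (first or second molars), based on statistical sample calculation".
- **Sample size {14}** recognises that teeth of one patient are related: "This sampling will also allow the adjustment of the sample size for the intra-subject correlation of statistical units (teeth"). It gives no ICC and no design effect.
- **Sequence generation {16a}** describes 150 patients with 210 teeth, split into groups of 50 participants and 70 teeth. It also describes a list running from 1 to 210 in which each number stands for one participant, allocated by simple randomisation.
- **Sample size details** also says that age, gender, lesion size and other baseline characteristics will enter the analysis, "in order to confirm the randomization of groups and the possible confounding effect of these characteristics". No method is named.
- **Baseline analysis** states as a fact: "The three groups will be similar in terms of disease type and periapical lesion size". No stratification is described that would secure this.

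**The concern.** A Kruskal-Wallis test assumes independent observations. Here the observations are teeth, and 210 teeth in 150 patients cannot all come from different people. The protocol acknowledges the correlation when it discusses sample size, then names a primary test that has no place for it.

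If all teeth of a patient receive the same treatment, positive correlation within patients makes the group success rates vary more than the test supposes. The p-value is then too small, and power at 210 teeth is below the planned 80%. If teeth are allocated independently, this does not happen. The validity of the primary test therefore rests on a design feature that the protocol describes in two incompatible ways.

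A second, smaller matter is that the same test takes no covariates, so it cannot deliver the consideration of lesion size that the protocol promises.

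**Working it through.** **Inputs from the protocol.** 210 teeth, 150 patients (mean 210/150 = 1.4 teeth), 70 teeth per group, three groups, 5% level, 80% power, effect size 20%.

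**Inputs assumed.** The ICC (0.1, 0.3, 0.5) and the spread of teeth per patient. The main case is 90 patients with one tooth and 60 with two (90 + 120 = 210). First and second lower molars are eligible, so up to four teeth per patient are possible; a more uneven case is 130 patients with one tooth and 20 with four (130 + 80 = 210).

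**Step 1: the plan's own figure.** The base success rate is not given, so 210 cannot be reproduced uniquely. With the usual two-sided formula for two proportions, n = [1.96·√(2p̄q̄) + 0.842·√(p1q1 + p2q2)]² / 0.20²:
- 66% v 86% gives 70.4, so 71 per group and 213 in all.
- 67% v 87% gives 68.3, so 69 per group and 207 in all.
- 60% v 80% gives 82 per group and 246 in all.

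A figure near 210 is thus reachable from some base rates. These calculations contain no allowance for clustering.

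**Step 2: the two descriptions of allocation.** If 210 entries are allocated singly, 70 to each group, two teeth of one patient fall in the same group with probability 69/209 = 0.33. Of 60 two-tooth patients, about 60 × 140/209 = 40 would have teeth in two groups. That cannot be squared with three groups of 50 whole participants. One of the two statements must give way.

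**Step 3: whole patients allocated.** With m teeth per patient, the design effect is DE = 1 + ICC × (Σm²/Σm − 1).
- Main case: Σm²/Σm = (90 + 240)/210 = 1.571, so DE = 1 + 0.571 × ICC.
- Uneven case: Σm²/Σm = (130 + 320)/210 = 2.143, so DE = 1 + 1.143 × ICC.

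The three-group test refers its statistic to chi-square with 2 degrees of freedom, for which P(χ² > x) = exp(−x/2). The true level is therefore 0.05^(1/DE).

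| ICC | DE (main) | True level | Effective teeth 210/DE | Teeth needed 210 × DE | DE (uneven) | True level |
|---|---|---|---|---|---|---|
| 0.1 | 1.057 | 5.9% | 199 | 222 | 1.114 | 6.8% |
| 0.3 | 1.171 | 7.8% | 179 | 246 | 1.343 | 10.7% |
| 0.5 | 1.286 | 9.7% | 163 | 270 | 1.571 | 14.9% |

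A simulation (20,000 runs per setting, success 75%, beta-binomial) agrees: 5.7%, 7.9% and 9.8% in the main case, and 6.9%, 10.5% and 14.9% in the uneven case. Taking 66% v 86% as an example, pairwise power with 70 teeth per group is 79.8% without clustering. It falls to 77.5%, 73.1% and 69.0% at the three ICCs in the main case.

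**Step 4: teeth allocated independently.** Under the null hypothesis the labels are then dealt out at random over teeth whatever the outcomes are, so correlation between teeth does not disturb the distribution of the test statistic. The same simulation gives 5.0%, 5.1% and 4.7% in the main case and 4.7% throughout in the uneven case.

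**Step 5: covariates.** Kruskal-Wallis has no covariate term. Under simple randomisation, leaving out lesion size does not alter the type I error. The loss is in precision, and it depends on how strongly lesion size predicts healing, which the protocol does not say.

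**The case against.** The strongest counter-argument is that the error rate is not shown to be wrong at all. On the reading in which the 210-number list allocates teeth, the named test holds its level. On the other reading, the inflation at an ICC of 0.1 is less than one percentage point, and both the ICC and the split of teeth per patient are assumptions. This stands, and it makes the point conditional. It does not remove it: the protocol's group sizes support patient-level allocation, and the protocol itself says the correlation exists.

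A reader might infer several stronger things that the documents do not support.

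- **That the test errs the other way if teeth are allocated.** Step 4 shows no material effect. A markedly conservative test would need a patient's teeth to be split between groups by rule, and no such rule is stated.
- **That omitting lesion size or centre makes the error rate wrong.** It does not under simple randomisation. As allocation is not stratified by centre, a centre term is a reasonable preference, not a correction.
- **That the protocol plans baseline tests followed by a data-driven choice of covariates.** It states an intention to consider them and gives no testing or selection rule. The entry "N/A. No additional analyses are planned" concerns subgroup and similar analyses and does not cancel that intention.
- **That Kruskal-Wallis is invalid for a binary outcome.** On binary data its statistic equals Pearson's chi-square times (N − 1)/N. The fault lies in the independence assumption and the lack of covariates.

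Model details are commonly left to an analysis plan. Here, however, the protocol has already named a primary test, and that choice is in question.

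**Conclusion.** The point holds in conditional form. The named primary test ignores a correlation that the protocol acknowledges, and the protocol does not settle whether that is harmful. If patients are randomised, the true level is about 5.9% to 9.7% for ICCs of 0.1 to 0.5 with one or two teeth per patient, and up to 14.9% in the uneven case. If teeth are randomised independently, it is about 5%. These sizes rest on an assumed ICC and an assumed spread of teeth.

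The inability to use lesion size is a gap between what is promised and what the test can do. Its cost is precision, of an amount that cannot be computed from the document. The statement that groups will be similar in lesion size is an expectation that simple randomisation does not guarantee.

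**What to change.** 1. In Sequence generation {16a}, state whether the patient or the tooth is randomised, and make the list length and group sizes agree with that.
2. Replace Kruskal-Wallis for success by one prespecified binary model on teeth with patient as cluster and robust variance. Generalised estimating equations would serve, either with identity link or with logit link and standardised risk differences; choose one beforehand. Include treatment group and baseline lesion diameter, with centre optional.
3. Report between-group risk differences with 95% confidence intervals. Keep a single global test of the three groups or name the primary contrast, so that moving to pairwise estimates does not open a multiplicity question.
4. State the ICC and design effect behind 210, or say that none was applied.
5. Drop the aim of confirming the randomisation from baseline data, and reword the similarity statement as a description of baseline characteristics by group.

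The cost is wording and a standard procedure. Lesion diameter is already measured at entry, since eligibility depends on it. Intervals become slightly wider where clustering is positive. The model remains sound whichever unit is randomised.

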### Criteria for discontinuing or modifying allocated interventions {11b}

(1) The presence of serious adverse events that doctors believe should lead to termination of trial participation, such as severe internal or external root resorption and tooth fracture; (2) poor clinical compliance; and (3) withdrawal of consent for study participation by the patient.

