### Outcomes {12}

All the steps of clinical examination will be carried out by the two examiners responsible for the study. Imaging evaluation will be done by other 2 specialists in Endodontics and 1 radiologist. All are with at least 15 years of experience.

Assessments will also be carried out at 6 (IOPAR), 12 (IOPAR), and 24 (CBCT) months for analysis of the tissue repair process. The therapeutic effect evaluation criteria are the following: (1) success: after RCT, the tooth should be asymptomatic, without fistula, without pain on percussion and palpation tests, without edema and in normal chewing function, radiographically in the process of periapical lesion regression from the first assessment (time point) at 06 months, and fully repaired after 2 years with confirmation through CBCT; and (2) failure: after RCT, the tooth is symptomatic, with symptoms of apical infection such as pain and fistula. The radiographic examination demonstrates the absence of decreased apical lesion or an enlarged apical lesion [22, 23].

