### Methods in analysis to handle protocol non-adherence and any statistical methods to handle missing data {20c}

Protocol violations after randomization will be listed in the clinical study report, tabulated by subject and recruitment site. We will perform intention-to-treat analyses with a “missing=failure” strategy to the management of missing data.

Sensitivity analyses will be performed for the missing data management: multiple imputation, available data, and maximum bias.

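### Two conflicting missing-data rules (LOCF and missing=failure) are set for the same 24-month success comparison, and LOCF does not fit an endpoint that needs two years and CBCT

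*Protocol article*

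**What the plan says.** Two sections of the protocol article each prescribe a way to fill missing outcomes.

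- Main outcome analysis, directly after the test for success rates: "For the missing data, the last observation carried forward (LOCF) method will be adopted to fill the validity analysis". The term *validity analysis* is not defined anywhere.
- Section {20c}: "We will perform intention-to-treat analyses with a “missing=failure” strategy to the management of missing data". It then continues: "Sensitivity analyses will be performed for the missing data management: multiple imputation, available data, and maximum bias". Neither LOCF nor missing=failure is in that list.

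The endpoint is described in Outcomes {12}. The assessment schedule is "Assessments will also be carried out at 6 (IOPAR), 12 (IOPAR), and 24 (CBCT) months for analysis of the tissue repair process". Success requires, besides clinical signs, that the tooth be "fully repaired after 2 years with confirmation through CBCT". Before that final verdict, the earlier films need only show it "radiographically in the process of periapical lesion regression from the first assessment (time point) at 06 months". Sample size details adds that follow-up of at least two years is needed to judge success or failure, and that after the first year "it is still possible to observe the presence of periapical radiolucency in 52 to 84% of cases".

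Section {11b} lists serious adverse events that end participation, "such as severe internal or external root resorption and tooth fracture". Neither missing-data passage says how those teeth are scored.

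**The concern.** A tooth with a favourable 12-month film and no 24-month CBCT may count as a success under one section and must count as a failure under the other. The headline success rate in each arm, and possibly the difference between arms, would then depend on which section the analyst follows. That choice should not be open once data are in hand.

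LOCF has a second problem. It treats an interim reading as if it were the final verdict, although the protocol itself says the verdict cannot be given before two years. It also replaces CBCT with a two-dimensional film, which the Discussion describes as masking results. A lesion that is shrinking but still visible at 12 months meets neither the definition of success nor that of failure in Outcomes {12}, so the plan does not fix what value LOCF would carry.

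**Working it through.** **Inputs from the article.** There are 70 teeth per arm (210 in three equal groups, Sequence generation {16a}). Radiolucency is still present after year 1 in 52 to 84% of cases (Sample size details), so 1 − 0.84 = 0.16 to 1 − 0.52 = 0.48 are free of it. The article gives no figure for missing data, so there is no stated value to reproduce. The 210 teeth enter only as the denominator.

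**Assumptions.** The missing share d is 10%, 20% or 30%. True 24-month success p is 80%, the same in missing and observed teeth. Every missing tooth has a 12-month film. The 16 to 48% range, which comes from cited studies, is taken to apply to those films.

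**Formula.** Let q be the share of missing teeth that the rule counts as success. Then

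reported success = p(1 − d) + d·q.

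Missing=failure sets q = 0. The gap between the rules is d·q, whatever p is. The bias of LOCF against the truth is d(q − p).

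**Gap between the rules, per arm.**

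| Missing | Teeth | Strict: complete 12-month repair needed (q = 0.16 to 0.48) | Upper bound: every carried tooth a success (q = 1) |
|---|---|---|---|
| 10% | 7 | 1.1 to 3.4 teeth = 1.6 to 4.8 points | 7 teeth = 10 points |
| 20% | 14 | 2.2 to 6.7 teeth = 3.2 to 9.6 points | 14 teeth = 20 points |

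Under the strict reading at 20% missing, about 7 to 12 of the 14 teeth are failures under both rules.

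**Direction of the LOCF bias, with p = 80%.**

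| Missing | Missing=failure | LOCF strict | LOCF with regression carried as success (q assumed 0.8 to 1.0) |
|---|---|---|---|
| 10% | 72% | 73.6 to 76.8% | 80 to 82% |
| 20% | 64% | 67.2 to 73.6% | 80 to 84% |
| 30% | 56% | 60.8 to 70.4% | 80 to 86% |

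At 20% missing the LOCF bias is 0.20 × (0.16 − 0.80) = −12.8 points to 0.20 × (0.48 − 0.80) = −6.4 points under the strict reading. It is 0 to +4 points if regression counts as success.

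**Unequal loss.** Take two arms with the same true success of 80% and 70 teeth each, compared by a pooled two-sided z-test that treats teeth as independent. This is an illustration, not the planned Kruskal-Wallis test.

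| Loss | Missing=failure | LOCF, q = 0.48 | LOCF, q = 0.90 |
|---|---|---|---|
| 10% v 20% | 8.0 points (p = 0.31) | 3.2 (p = 0.66) | −1.0 (p = 0.88) |
| 10% v 30% | 16.0 points (p = 0.049) | 6.4 (p = 0.39) | −2.0 (p = 0.76) |

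The rule changes the size and can change the sign of the difference. It changes significance only under the strong 10% v 30% imbalance, and then barely.

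**Cost of missing=failure.** With equal loss d in both arms, a true difference is multiplied by 1 − d: 20 × (1 − 0.20) = 16 points. In a trial labelled non-inferiority, such shrinkage makes arms look more alike.

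**The case against.** The best defence is that *validity analysis* may denote a separate analysis set, so that LOCF and missing=failure serve different purposes, and that the planned sensitivity analyses would expose any dependence on the rule. The first part is a guess, since no sentence defines the term or assigns LOCF to another set. The second part is partly right: the sensitivity analyses would show the dependence, but they do not say which result is the main one. Nor is this a detail left to a fuller document. The article states both rules, and they conflict.

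Four stronger readings are tempting, and the article does not support them.

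- A reader might infer that the rules differ for every tooth without a 24-month CBCT. They do not: a tooth last seen unhealed, or lost before six months with only its baseline lesion to carry, fails under both.
- A reader might infer that LOCF always hides failures. That needs a regressing lesion to be scored as success. Under the strict definition LOCF lowers the success rate, because lesions that would have healed by 24 months are frozen as unhealed.
- A reader might take 20 points as the expected discrepancy. It is an upper bound at an assumed 20% loss, with every carried tooth counted as a success.
- A reader might infer that LOCF is specified to credit fractured teeth with their last good image. The article does not say that such teeth are treated as missing. The fracture could itself be the last observation, since success requires normal chewing function and adverse events are recorded. What stands is that their classification is open.

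**Conclusion.** The conflict is real and lies in the current text: two rules for one success comparison, neither ranked and neither labelled as sensitivity. LOCF is also unsuited to the endpoint on the protocol's own account of how long healing takes and how it is confirmed.

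The size depends on a dropout rate that the article does not give, although its Discussion expects long follow-up to be difficult. At an assumed 20% missing the rules differ by about 3 to 10 points per arm on the strict reading, and by at most 20. At 10% missing the figures are about 2 to 5, and at most 10. The strict range assumes that all missing teeth have a 12-month film; losses before six months would narrow it. For scale, the sample size rests on an effect size of 20%, whose scale is not stated. The direction of LOCF bias is not fixed. The point must be settled before analysis because the main result depends on it.

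**What to change.** 1. Delete the LOCF sentence under Main outcome analysis and state one rule for the 24-month success comparison. The missing=failure rule already in section {20c} is one candidate.
2. If that rule is kept, report the multiple imputation already planned in {20c} alongside it, because of the shrinkage toward no difference.
3. State how teeth discontinued for fracture or severe resorption are classified in the analysis, so that an earlier film is not carried forward for them. Sections {11b}, Outcomes {12}, Main outcome analysis and {20c} must be reconciled on this point.

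The cost is a change of wording in the protocol and analysis plan, made before the 24-month data are analysed. No extra visits, images or teeth are needed, the conduct of the trial is unchanged, and the multiple imputation is already planned.

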#### Secondary outcome analysis

Intra-group and inter-group comparisons for analysis of postoperative pain and post-treatment satisfaction will be performed by Friedman and Kruskal-Wallis tests, respectively. Inter-group comparisons for preferences regarding to the number of clinical visits will be performed by the chi-square test. All tests will be performed at 5% of the level of significance.

